## Abstract

**Rationale:**

The effectiveness of universal immunisation with pneumococcal conjugate vaccine (PCV) has been evident in many countries. However, the global impact of PCV is limited by its cost, which has prevented its introduction in several countries. Reducing the cost of PCV programmes may facilitate vaccine introduction in some countries and improve the sustainability of PCV in EPIs in low-income countries when they transition away from subsidised vaccine supply.

**Methods and design:**

PVS is a real-world field trial of an alternative schedule of one dose of PCV scheduled at age 6 weeks with a booster dose at age 9 months (i.e. the alternative ‘1+1’ schedule) compared to the standard schedule of three primary doses scheduled at 6, 10, and 14 weeks of age (i.e. the standard ‘3+0’ schedule). Delivery of the interventions began in late 2019 in 68 geographic clusters and will continue for 4 years. The primary endpoint is the prevalence of nasopharyngeal vaccine-type pneumococcal carriage in children aged 2–260 weeks with clinical pneumonia in year 4. Secondary endpoints are the prevalence of vaccine-type pneumococcal carriage among all ages in year 4 and the incidence of radiological pneumonia in children enrolled to receive the interventions. Additional disease and carriage endpoints are included.

**Purpose:**

This statistical analysis plan (SAP) describes the cohorts and populations, and follow-up criteria, to be used in different analyses. The SAP defines the endpoints and describes how adherence to the interventions will be presented. We describe how analyses will account for the effect of clustering and stratified randomisation. The SAP defines the approach to non-inferiority and other analyses. Defining the SAP early in the trial will avoid bias in analyses that may arise from prior knowledge of trial findings.

**Supplementary Information:**

The online version contains supplementary material available at 10.1186/s13063-022-06900-x.

## Introduction

This statistical analysis plan follows the reporting guidelines described by Rodriguez et al. [1] and the UK Clinical Research Collaboration Registered Clinical Trial Unit Statisticians’ Operational Group [2], as well as CONSORT guidelines for reporting cluster-randomised [3] and non-inferiority [4] trials. The trial protocol is available on the *Trials* website [5].

The following terminology is used to refer to the analysis populations/cohorts and types of analyses:Individual-level cohort—participants enrolled as infants at Expanded Programme on Immunisation (EPI) clinics to receive the trial interventionsIndividual-level analysis—approach to regression analysis of cluster-randomised trials including data on individual participants while also accounting for cluster-level correlationCluster-level analysis—approach to regression analysis of cluster-randomised trials that summarises data at the cluster-level which is then used in a further step to estimate the intervention effectPopulation-level population/cohort—all resident children, assigned to each group according to village of residence, under surveillance for endpoints, and included in analysis regardless of enrolment as an infant to receive the study intervention

### Background and rationale

The Gambian Expanded Programme on Immunisation (EPI) introduced the 7-valent pneumococcal conjugate vaccine (PCV7) in 2009 and PCV13 in 2011, using the standard schedule of three doses in early infancy. Compared to the pre-vaccine period, in 2016–2017, there was a 92% reduction in the incidence of vaccine-type (VT) invasive pneumococcal disease (IPD) in the 2–59-month age group [6]. PCV also prevents the acquisition of VT pneumococcal carriage, with resulting indirect herd protection effects in the population. However, the prevalence of nasopharyngeal (NP) carriage of VT pneumococci in young children remains around 15% (author’s own data), having fallen from 47% in the pre-vaccine period [7]. The global impact of PCV is limited by its cost, which has prevented its introduction in several countries. Reducing the cost of PCV programmes may facilitate vaccine introduction in some countries and improve the sustainability of EPI programmes in low-income countries when they transition away from subsidised vaccine supply through Gavi, the Vaccine Alliance.

This pragmatic cluster-randomised, non-inferiority field trial is being conducted in the Basse and Fuladu West Health and Demographic Surveillance Systems (BHDSS and FWHDSS) in rural Gambia. Cluster-wise delivery of the schedules at EPI clinics over 4 years in distinct geographic populations will allow direct and indirect effects of the schedules on pneumococcal transmission and disease to develop within each geographic population cluster. Because the incidence of IPD and radiological pneumonia has fallen greatly with PCV vaccination, such endpoints cannot be primary endpoints in this trial. We have chosen NP carriage of VT pneumococci in children with clinical pneumonia as the primary endpoint. Disease measures are included, primarily related to safety. We also include a number of additional pneumococcal carriage endpoints at the community-level.

Using the framework of Halloran et al., for study designs to measure different effects of vaccines and vaccination [8], this trial aims to estimate and compare the overall public health effects of the two PCV schedules. Overall public health effects include the indirect effects of widespread vaccination on unvaccinated individuals [8]. The combination of direct and indirect effects of widespread vaccination on vaccinated individuals is termed the total effects of vaccination and vaccination programme. The overall public health effects of the vaccination programme depend on the weighted average of indirect effects on unvaccinated individuals and the total effects on vaccinated individuals [8].

The primary endpoint analysis will use the population-level population with observations in year 4 after the development of the direct and indirect effects of the schedules (Table 1). All children aged 2–260 weeks with clinical pneumonia in year 4, and resident in the trial area, whether enrolled to receive trial interventions or not, will be included in the analysis. The analysis will provide information combining the direct and indirect effects of the PCV schedules on VT pneumococcal transmission with interpretation related to the individual resident child.

**Table 1 Tab1:** Analysis framework for populations/cohorts, observations/follow-up, and outcome measures

Endpoint Designation	Population/cohort	Observation/follow-up	Endpoint	Effect measure
Primary	^a^Resident children and clinical pneumonia	Continuous surveillance	^b^VT carriage	Prevalence ratio
Secondary	^c^Enrolled children	^d^Intention-to-treat	Radiological pneumonia	Incidence ratio
	All resident population	Cross-sectional	^e^VT carriage	Prevalence ratio
Tertiary	^a^Resident children and clinical pneumonia	Continuous surveillance	^f^NVT and ^g^Spn carriage	Prevalence ratio
	Age 6–12 weeks no PCV	Cross-sectional	^h^VT carriage	Prevalence ratio
	^c^Enrolled children and clinical pneumonia	^d^Intention-to-treat	VT, NVT, and ^g^Spn carriage	Prevalence ratio
	^i^Enrolled children received intervention and clinical pneumonia	^§§^Per-protocol	VT, NVT, and ^g^Spn carriage	Prevalence ratio
	Resident children	Continuous surveillance	VT, NVT, and ^g^Spn IPD	Incidence ratio
	“	“	Radiological pneumonia	“
	“	“	Clinical pneumonia	“
	“	“	Clinical pneumonia and VT carriage	“
	“	“	Hypoxic pneumonia	“
	“	“	Hospitalisation	“
	“	“	Mortality	“
	Enrolled children	^d^Intention-to-treat	VT, NVT, and ^g^Spn IPD	“
	“	“	Clinical pneumonia	“
	“	“	Clinical pneumonia and VT carriage	“
	“	“	Hypoxic pneumonia	“
	“	“	Hospitalisation	“
	“	“	Mortality	
	Enrolled children received intervention	^j^Per-protocol	Radiological pneumonia	“
	“	“	VT, NVT, and Spn IPD	“
	“	“	Clinical pneumonia	“
	“	“	Clinical pneumonia and VT carriage	“
	“	“	Hypoxic pneumonia	“
	“	“	Hospitalisation	“
	“	“	Mortality	“

^a^Population-based population aged 2–260 weeks. ^b^Primary endpoint specified in year 4 and also calculated as tertiary endpoints in years 1, 2, and 3. ^c^Cohort enrolled to receive interventions. ^d^Events counted from enrolment to end of follow-up. ^e^Secondary endpoint specified in year 4 and also calculated as a tertiary endpoint in year 3 (all ages and age-stratified). ^f^Calculated in years 1, 2, 3, and 4. ^g^Spn = all pneumococcal carriage. ^h^In year 4. ^i^Cohort enrolled and received interventions PP. ^j^Events counted from 14 days post-PCV1 to end of follow-up

The trial includes two secondary endpoints (Table 1). The secondary endpoint of radiological pneumonia incidence will include all children enrolled to receive the interventions and function primarily as a safety endpoint. This individual-level cohort will experience the direct effects of the different PCV schedules and their increasing indirect effects over 4 years. The radiological pneumonia endpoint offers reasonable specificity [9] to detect a potential difference in the incidence of this important disease endpoint. However, limited frequency and statistical power precludes specification of a non-inferiority hypothesis for this endpoint. We will present a point estimate and confidence interval indicating the potential range of values of the incidence rate ratio of radiological pneumonia in the two groups. An additional secondary endpoint will be VT pneumococcal carriage at the community-level in all ages in year 4. This population-level measurement of VT carriage will include direct and indirect effects after 4 years of intervention delivery in the population.

Tertiary endpoints will include year 4 measurement of VT carriage in 6–12-week-old infants who have not yet been immunised with PCV. This analysis will relate only to indirect effects in this important age group. Endpoints specifying non-vaccine type (NVT) pneumococcal carriage will compare the effects of the schedules on potential ‘serotype replacement’ in carriage that follows vaccine-induced reductions in VT carriage. Additional disease endpoints will further inform the safety of the alternative schedule (Table 1). Specification of multiple complementary endpoints means that overall interpretation of the trial results will require synthesis of all the available information.

Analyses using the population-level population will compare the impact of the schedules relating to the total population, as is appropriate for decision-making in mature immunisation programmes. Analyses will also be conducted in the individual-level cohort enrolled to receive the intervention. Individual-level cohort analyses will provide information on the biological effects of the schedules, particularly related to the relative safety of the two schedules that can most easily be interpreted in the light of the wide range of settings where the schedules could be used. Differences between per-protocol (PP) and intention-to-treat (ITT) analyses of the individual-level cohort will relate mainly to delays of receipt of scheduled doses and incorrect administration of schedules, which will differ from one setting to another.

The setting is a rural African location where over 75% of vaccination is provided through outreach visiting villages only once per month. The age at vaccination may therefore be different from that which applies in urban African settings, where vaccination may be more frequently available. The conduct of the trial has enhanced service delivery for the primary series of doses by a marginal degree so the age at vaccination in the trial is largely representative of the situation that would pertain should the alternative schedule be introduced in the routine EPI. However, the timing and coverage of the PCV booster dose at 9 months of age may have been enhanced to some degree. Thus, ITT analysis using the individual-level cohort will show the impact of the alternative schedule under a particular set of vaccination delivery circumstances that may not represent a routine setting. Analysis in the population-level population most clearly defines the conditions needed to combine all direct and indirect effects of the schedules in the population. The individual-level cohort PP results can most easily be compared between different study sites. The trial will include mathematical modelling of schedule effects on VT carriage with varied coverage of the alternative schedule PCV booster dose. Table 1 presents the analysis framework, specifying the populations and cohorts, observations and follow-up, endpoints, and effect measures.

### Objectives

The trial aims to account for the direct and indirect effects of vaccination with PCV13 at the population-level. We aim to test whether transition from the standard schedule to an alternative schedule, with doses scheduled at 6 weeks and 9 months of age, is non-inferior to continued use of the standard scheduling of doses at 6, 10, and 14 weeks of age.

#### Endpoints

Primary endpointPrevalence of NP carriage of VT pneumococci in children aged 2–260 weeks with clinical pneumonia in year 4

Secondary endpointsIncidence of radiological pneumonia in children enrolled to receive interventionPopulation-based NP carriage prevalence of VT pneumococci year 4 (tertiary endpoint year 3)

Tertiary endpointsPrevalence of NP carriage of NVT and all pneumococci in children aged 2–260 weeks with clinical pneumonia in year 4Prevalence of NP carriage of VT, NVT, and all pneumococci in unimmunised infants aged 6–12 weeks in year 4Prevalence of NP carriage of VT, NVT, and all pneumococci in enrolled children (and children who received intervention) with clinical pneumoniaIncidence of VT, NVT, and all IPD in resident children aged 2–260 weeksIncidence of radiological pneumonia in resident children aged 2–260 weeksIncidence of clinical pneumonia in resident children aged 2–260 weeksIncidence of clinical pneumonia associated with NP carriage of VT pneumococci in resident children aged 2–260 weeksIncidence of hypoxic pneumonia in resident children aged 2–260 weeksIncidence of hospitalisation in resident children aged 2–260 weeksIncidence of mortality in resident children aged 2–260 weeksIncidence of VT, NVT, and all IPD in enrolled children and enrolled children who received interventionIncidence of radiological pneumonia in enrolled children and enrolled children who received interventionIncidence of clinical pneumonia in enrolled children and enrolled children who received interventionIncidence of clinical pneumonia associated with NP carriage of VT pneumococci in enrolled children and enrolled children who received interventionIncidence of hypoxic pneumonia in enrolled children and enrolled children who received interventionIncidence of hospitalisation in enrolled children and enrolled children who received interventionIncidence of mortality in enrolled children and enrolled children who received intervention

#### Other analyses

The first endpoint below aims to detect potential early impact of the alternative schedule:Prevalence of NP carriage of VT pneumococci in children aged 2–260 weeks with clinical pneumonia in year 2Incidence of non-pneumococcal invasive bacterial disease, presentations with diarrhoea, presentations with cough or cold/upper respiratory tract infection, hospitalisations with diarrhoea, and proportion of clinical pneumonia patients who are hospitalised (analyses to detect potential differential case ascertainment or access to care)

## Study methods

### Trial design

This is a cluster-randomised, non-inferiority, parallel-group, unmasked field trial under real-world conditions. This rural Gambian population is the same as that included in an earlier trial that established the efficacy of PCV9 [9] and effectiveness of routine infant vaccination with PCV13 [6, 10, 11]. The schedule tested in the PCV9 trial (doses scheduled at 6, 10, 14 weeks of age) is the same as the standard schedule in this non-inferiority trial. Efficacy of PCV9 was established using the endpoint of radiological pneumonia while the primary endpoint in this trial is VT carriage prevalence in children with clinical pneumonia. This trial includes radiological pneumonia as a secondary (safety) endpoint.

#### Definition of cluster and design application to clusters

The trial area of the BHDSS and FWHDSS consists of 68 contiguous geographic units within which resident infants are assigned to attend the one EPI clinic in that geographic area. All the geographic clusters in the BHDSS and FWHDSS were eligible for the trial. The geographic clusters of villages were mapped and designed to minimise the interaction of children in different clusters through school attendance. The average cluster population is 4000, although with significant variability. Group allocation of infants enrolled at EPI clinics is determined by the allocation of the village of residence.

#### Trial design

Each cluster is randomly allocated, in a 1:1 ratio, to one of two study groups. Infants who have not completed their PCV schedule and are aged <9 months are allocated to receive either the alternative or standard PCV schedule. The alternative schedule specifies eligibility for doses at 6 weeks and 9 months of age. The standard schedule specifies eligibility for doses at 6, 10, and 14 weeks of age. This design permits the estimation of the combined direct and indirect effects at the population-level.

### Randomisation

An independent statistician prepared the randomisation lists. All clusters were randomised at the beginning of the trial using a blocked scheme to ensure similar numbers of clusters were assigned to each group. Randomisation was stratified by (1) location (BHDSS or FWHDSS) and (2) a binary variable of ‘high’ or ‘low’ cluster-level incidence of clinical pneumonia (which correlates with VT pneumococcal carriage prevalence). Randomisation was carried out using the above stratification until restricted selections were achieved in which Basse and Bansang towns were in either trial group (the only two hospitals in the trial area are in Basse and Bansang), there was a balance in terms of the presence of a health facility in allocated clusters (i.e. six in one group and five in the other group), and there was balance on total population size between the two groups (i.e. <10% difference in the two groups). Random allocation was performed and revealed in a public event in which one of 100 valid randomisation lists was randomly selected.

All resident infants are eligible for enrolment in the trial, according to the cluster allocation of their village of residence. Consent is sought for the enrolment of infants at EPI clinics to receive the interventions. Consent is also sought for the investigation of patients presenting to health facilities who are under surveillance for clinical endpoints, and also from pneumococcal carriage survey participants.

### Sample size

#### Non-inferiority margin

We determined the non-inferiority margin using the concept of ‘largest loss of impact of the current treatment that would be clinically acceptable’, an approach recommended by the US FDA [12]. The non-inferiority margin uses a relative metric as the relative effect of the standard schedule is likely to be constant [13]. The introduction of the standard schedule has reduced NP VT prevalence in children from 47 to 13%, i.e. a 72% reduction (author’s own data). Baseline risk may change over time, so an absolute value for the non-inferiority margin may not provide a reliable measure of the difference in impact of the two schedules.

Given the advantages of the alternative schedule, the non-inferiority margin will be a 15% loss of the impact of the standard schedule; this value is supported by empiric survey data. In March 2017, an online survey was sent to 72 individuals involved in pneumococcal vaccine research, policy, and clinical care. Valid responses were received from 19 respondents. The survey question presented 10 hypothetical results of VT prevalence in the two trial groups, on a scale of increasing ‘loss of impact’ associated with the alternative schedule, from a baseline of no loss (i.e. a 0% loss of impact) up to a 50% loss of impact. Respondents were asked to consider themselves as decision-makers in their national immunisation programmes, requested to consider a change to their national programme from the standard to the alternative schedule based on the results of the trial. Respondents selected one option corresponding to the ‘loss of impact’ which would sway their decision against introducing the alternative schedule. Using the metric of a percentage loss of impact of the standard schedule which would sway decisions against the new schedule the mean value was a 22.2% loss of impact. The results of the survey support use of a non-inferiority margin that the alternative schedule be associated with a ≤15% loss of impact compared to the standard schedule.

The prevalence of NP carriage of VT pneumococci in the BHDSS among young children with clinical pneumonia from Jan–Sept 2015 was 17% and fell to 15% in Oct–Dec 2015. Assuming VT prevalence of 13% in the standard schedule group at the end of the trial, a 15% loss of impact translates to prevalence in the alternative schedule group of (1 − [0.72 − (0.72 × 0.15)]) × 47% = 18.3%. The non-inferiority margin is expressed in terms of the prevalence ratio outcome measure as 18.0/13.0= 1.38. We used changes in VT prevalence to inform the non-inferiority margin because reductions in VT carriage following the introduction of PCV can predict the impact of PCV on IPD [14] and because carriage prevalence is proportional to the rate of pneumococcal transmission.

For the secondary endpoints of VT pneumococcal carriage prevalence in population-based surveys and among infants aged 6–12 weeks unimmunised with PCV, we will also use the non-inferiority margin of a ≤15% loss of impact in the alternative compared to standard schedule.

#### Sample size calculation

Sample size calculations were based on the primary outcome of NP carriage of VT pneumococci in children aged 2–260 weeks with clinical pneumonia. Initial sample size calculations assumed an equal number of 60 participants measured for the primary endpoint in each cluster, that is, 2040 in each group and 4080 in total. Using Basse data from 2015, we assumed the prevalence of VT carriage to be 13% in both the standard and alternative schedule groups. The alternative schedule will be considered non-inferior if the upper limit of the two-sided 95% confidence interval for the prevalence ratio is ≤1.38 (0.18/0.13 = 1.38). Using Basse data, we estimated the intra-class correlation coefficient (ICC) to be 0.01–0.02. We calculated study power using the methods of Farrington et al. [15] and Donner et al. [16]. Using the more conservative value for ICC of 0.02, a minimum number measured for the primary endpoint per cluster of 60, with 34 clusters per arm (with design effect of 2.18) and *α*=0.05, a sample size of 2040 per arm will provide 93% power to test the non-inferiority of the alternative schedule.

To increase confidence in the study power, we simulated data using 2015 BHDSS data on cluster-wise VT carriage prevalence in children with pneumonia. The simulated data were designed to be similar to the villages included in this trial with respect to the mean carriage prevalence, as well as the variability in prevalence across clusters. Using 1000 simulated populations, each consisting of 68 clusters of 60 individuals, baseline prevalence of 10% and a largest acceptable increase of 4%, i.e. from 10% to 14% (i.e. non-inferiority prevalence ratio of 0.14/0.10=1.40), study power was ≥85% in most scenarios.

During the piloting of trial procedures, it became clear that the number of patients measured for the NP carriage endpoint would be quite variable among clusters with less than 60 patients in some clusters. Further simulations using local data on the variable numbers expected per cluster in 1 year (*N*=3948, median=33, range 7–506) and assuming VT prevalence of 16% in both groups demonstrated trial power of 90%. In order to maximise trial power, the primary outcome will be measured in all eligible patients in each of the 68 clusters with a total number ≥4080 included in the final year 4 analysis.

In the community carriage surveys in years 3 and 4, we will sample 60 residents in each of the 68 clusters. The same assumptions and methods of power calculation as for the primary endpoint will apply. We assume ICC=0.02, 15% baseline VT carriage prevalence in both groups, and a ≤1.38 prevalence ratio derived from the non-inferiority margin of a ≤15% ‘loss of effect’ compared to the standard schedule. If the upper bound of the 95% confidence interval of our prevalence ratio comparing the alternative to the standard schedule clusters is ≤1.38, then the alternative schedule will be considered non-inferior. Following these assumptions, the community carriage surveys in years 3 and 4 will have power >94% if we collect 4080 samples evenly across 68 clusters (i.e. 60 per cluster).

Power for the tertiary endpoint of VT prevalence in PCV unimmunised infants aged 6–12 weeks (assume VT carriage prevalence of 10%) will be similar to that for the primary endpoint. The study is not powered to determine non-inferiority for other endpoints.

As opposed to the non-inferiority hypothesis that is specified for the primary endpoint in year 4, we will specify a superiority hypothesis for the analysis of year 2 data on VT prevalence in children with clinical pneumonia. Setting a 5% level of significance with a two-sided test, power of 80%, with ICC=0.02, and assuming prevalence of VT carriage in the control group is 22%, we wish to detect an absolute difference of ≥7%. That is, the smallest clinically significant difference that we wish to detect is equivalent to prevalence of 15% versus 22% in the two groups and a prevalence ratio of 15.0/22.0=0.68. Given these parameters, if we measure the endpoint in 25 individuals per cluster, we would need to include 29 clusters in each group, that is, a total of 58 clusters. We will measure the endpoint in all 68 clusters using all the available measurements of the endpoint in year 2.

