## Statistical principles

### Confidence intervals and p-values

#### Level of statistical significance

The level of statistical significance for all non-inferiority hypotheses will be set at an α-level of 0.05 using two-sided significance tests [18, 19]. We specify a two-sided α-level of 0.05 as we wish to know the lower, as well as upper limit of the confidence interval around the effect estimates, as it is plausible that the alternative schedule may be superior to the standard schedule. For the superiority hypothesis concerning VT prevalence in children with clinical pneumonia in year 2, we will use a two-sided significance test with an α-level of 0.05.

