##### Other population-level endpoints

The population-level prevalence of VT pneumococcal carriage will be measured in years 3 and 4 using age-stratified random samples of all residents in the HDSS (Table 1). Age-stratified random samples of 60 participants will be selected in each cluster with a total sample size of 4080 in each year. Ten individuals in each randomly selected household will be randomly selected, 2:2:2:1:1:1:1 according to the age stratification (0–11 months, 12–23 months, 24–59 months, 5–9 years, 10–14 years, 15–44 years, and ≥45 years). The prevalence of VT carriage will be calculated for each cluster using the number of enrolled participants as the denominator.

The population-level prevalence of VT pneumococcal carriage in infants aged 6–12 weeks unimmunised with PCV will be measured in year 4 (Table 1). Eligible infants will be born to women resident in the HDSS, present to an EPI clinic, be 42–84 days of age, and not yet be immunised with a first dose of PCV. Sixty infants in each cluster will be randomly selected from eligible infants. The prevalence of VT carriage will be calculated for each cluster using the number of enrolled infants.

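### The power of over 94% for the all-age community survey rests on a 15% VT prevalence that the SAP supports only for young children

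*SAP article*

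**What the plan says.** All references are to the SAP article.

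- **Sample size calculation**, on the community surveys: "The same assumptions and methods of power calculation as for the primary endpoint will apply". It then gives the inputs, "We assume ICC=0.02, 15% baseline VT carriage prevalence in both groups", and the result, "the community carriage surveys in years 3 and 4 will have power >94% if we collect 4080 samples evenly across 68 clusters". The decision rule is stated as "If the upper bound of the 95% confidence interval of our prevalence ratio comparing the alternative to the standard schedule clusters is ≤1.38", in which case the alternative schedule is taken to be non-inferior.
- **Sample size calculation**, on the primary endpoint: VT prevalence is 13% in both groups, with ICC 0.02, 60 per cluster, 34 clusters per arm and a design effect of 2.18.
- **Background and rationale**: "carriage of VT pneumococci in young children remains around 15" per cent. **Non-inferiority margin** also reports 15%, for young children with clinical pneumonia in October to December 2015.
- **Other population-level endpoints**: individuals are sampled "2:2:2:1:1:1:1 according to the age stratification". Three strata lie below 5 years and four lie from 5 years upwards.
- **Timing of secondary endpoint assessments**: the survey endpoint covers all ages. Year 4 is the secondary endpoint and year 3 a tertiary one.

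**The concern.** The survey is planned at a prevalence that the SAP ties only to young children, although four in ten participants are older. It is also higher than the 13% assumed for under-fives with pneumonia, despite the statement that the same assumptions apply. The SAP explains neither point.

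This matters because the precision of a prevalence ratio depends directly on prevalence: fewer carriers give a wider interval against a fixed margin of 1.38. The year 4 survey carries a formal non-inferiority test (Population-level VT prevalence in the community). The planned summary figure will show only endpoints judged to have enough power (Presentation of results), and for this endpoint the claim of over 94% is the evidence of that. If the power is overstated, an upper limit above 1.38 is more easily misread as evidence against the schedule when it may only reflect low precision.

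**Working it through.** **Inputs from the SAP.** 34 clusters of 60 per arm, so 2040 per arm; ICC 0.02; margin 1.38; true ratio 1; two-sided 95% confidence interval.

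Design effect = 1 + 59 × 0.02 = 2.18. Effective n = 2040 / 2.18 = 935.8 per arm.

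**Age mix.** 2:2:2:1:1:1:1 sums to 10. Under 5 years: 6/10 = 60%. Aged 5 years or more: 4/10 = 40%. Pooled prevalence p = 0.6 × (under 5) + 0.4 × (5 or more).

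**Assumption, not in the documents.** VT prevalence at 5 years or more. With under-fives at 15%:
- older residents 15%: p = 0.090 + 0.060 = 15.0%
- older residents 10%: p = 0.090 + 0.040 = 13.0%
- older residents 5%: p = 0.090 + 0.020 = 11.0%

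**Formulas.**
- Log ratio: SE = √[2(1−p)/(p × 935.8)]; power = Φ(ln 1.38/SE − z).
- Difference: margin 0.38p; SE = √[2p(1−p)/935.8]; power = Φ(0.38p/SE − z).
- z = 1.960 (two-sided 5%) or 1.645 (one-sided 5%).

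**Reproducing the plan's figure at 15%.**
- Log ratio, two-sided: SE = √(2 × 5.667/935.8) = 0.1100; 0.3221/0.1100 = 2.927; Φ(2.927 − 1.960) = 83.3%.
- Difference: SE = √(2 × 0.1275/935.8) = 0.01651; 0.057/0.01651 = 3.453. Two-sided Φ(1.493) = 93.2%; one-sided Φ(1.808) = 96.5%.
- An ordinary two-proportion comparison of 15% with 20.7% (1.38 × 15%), one-sided 5%, gives 94.3%, the closest match to the stated figure.

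**Same methods at the lower pooled prevalences (power, %).**

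| Method, ICC 0.02 | p = 15% | p = 13% | p = 11% |
|---|---|---|---|
| Log ratio, two-sided 95% CI | 83.3 | 76.8 | 68.8 |
| Farrington–Manning ratio, two-sided | 83.0 | 76.6 | 68.7 |
| Log ratio, one-sided 5% | 90.0 | 85.3 | 78.9 |
| Difference, two-sided | 93.2 | 88.8 | 82.4 |
| Two proportions, p v 1.38p, one-sided 5% | 94.3 | 90.5 | 85.0 |
| Difference, one-sided 5% | 96.5 | 93.7 | 89.3 |

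The 13% column is also what the primary endpoint's own prevalence would give. Moving from 15% to 11% costs about 7 points on the most favourable method (96.5 to 89.3) and about 15 on the ratio scale (83.3 to 68.8).

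If under-fives are at 13% instead, older residents at 10% or 5% give p = 11.8% or 9.8%. Power is then 72.2% or 63.2% (log ratio, two-sided), and 91.3% or 85.6% (difference, one-sided).

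**Slack in the claim.** On the most favourable method, 94% power needs 0.38 × √[467.9 × p/(1−p)] = 1.645 + 1.555 = 3.200, so p is about 13.2%. With under-fives at 15%, older residents would have to carry VT at a little over 10%.

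**The case against.** The strongest reply is that nothing in the SAP shows 15% to be too high. A reader might infer that older residents carry VT less often and that the survey is therefore underpowered. The documents do not support that as a statement of fact: they give no VT prevalence from age 5 upwards and never say that it is lower. The SAP also uses several figures for children (13%, 15%, 16%, 17% and 22%), and some are compatible with a pooled 15%: 0.6 × 22% + 0.4 × 4.5% = 15.0%, or 0.6 × 16% + 0.4 × 13.5% = 15.0%. The link between the survey's 15% and the young-child figure is itself an inference from equal numbers. All of this stands, and it makes the effect on power conditional. It does not supply the missing justification, because the SAP makes no such argument.

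Second, the SAP reports simulations with 68 clusters of 60 at 10% prevalence. That is the survey's layout at a low prevalence. But they used data on children with pneumonia, a margin of 1.40 and observed cluster variability. They also yielded power of at least 85% in most scenarios, which does not establish a claim of over 94%.

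Third, a reader might attribute the whole fall from over 94% to 69% or 77% to prevalence. That would be wrong. The ratio-scale two-sided calculation gives only 83% at 15%, so that part of the gap comes from the scale and sidedness of the test, a separate matter. Only the movement along each row of the table belongs to this point.

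Fourth, at ICC 0.01 the difference-scale one-sided calculation still gives 95.9% at 11%. The SAP specifies 0.02 for this survey, so that does not rescue the stated figure.

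**Conclusion.** The point holds in a conditional form. The 15% is unsupported for a sample that is 40% aged 5 years or more, and it departs from the primary endpoint's 13% although the same assumptions are said to apply. At ICC 0.02, a pooled prevalence of 13% puts power below 94% on every method tried (76.6% to 93.7%), and 11% puts it at 68.7% to 89.3%. On the most favourable of these methods, at 13%, the shortfall is only 0.3 points. Under the SAP's own ratio rule with a two-sided 95% interval, power falls from 83% at 15% to 77% or 69%.

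These sizes rest on an assumed 10% or 5% in older residents, 15% in under-fives, equal clusters of 60 and no true difference between schedules. Whether 15% is actually too high cannot be settled from the SAP. The sample size, margin, model and decision rule are not affected.

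**What to change.** In the community survey paragraph of Sample size calculation, either give the source of the 15% for an all-age sample, or replace it with the prevalence implied by the 2:2:2:1:1:1:1 age mix. The year 3 survey, pooled over arms, could supply age-specific prevalence without revealing any difference between groups. Correct the statement that the primary endpoint's assumptions apply, since the prevalence differs. Then restate the survey power as a range over plausible pooled prevalences, at ICC 0.02 and under the two-sided 95% interval rule on the prevalence ratio.

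The cost is a short recalculation and a change of wording. No extra participants are needed; the downside is a less favourable stated power.
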